### Recruitment

Participants will be recruited for the study under the title “Mobile ECGs in Detection of Subclinical AFib in High-Risk Outpatient Populations.” Study participants will be approached by a research assistant trained in informed consent and will be asked if they are interested in learning more information about this study. If they are interested, the research assistant will discuss the goals of the study as well as potential risks. If the participant agrees to participate in the study, the research assistant will provide them with informed consent and a questionnaire for them to fill out that aims to reveal any risk factors for cardiovascular disease.

Participants enrolled in the study will receive a standardized data collection code in the format of “NEP,” the number of weeks, and the number of participants enrolled that week. For example, NEP0101 will indicate the first participant enrolled during the first week of the study. This will allow for participant data to remain confidential during the data analysis portion of the study. A master sheet of the collection codes and the associated participant study data will be stored on an institutional review board (IRB)–approved, secure study Dropbox.

### Procedure

Upon obtaining informed consent, research assistants will use the KardiaMobile single-lead ECG by AliveCor to obtain an ECG reading. Before conducting the examination or filling out a cardiovascular-specific screening survey, participants will have to consent to the study. Any questions regarding the survey will be answered by study personnel present in the room. The Mobile ECG recording by the KardiaMobile device will take place in the patient waiting room for approximately 30 seconds.

The smartphone single-lead attachment is compatible with the KardiaMobile app, a HIPAA (Health Insurance Portability and Accountability Act)-compliant smartphone phone app that can temporarily save these ECGs. Each ECG recorded from a participant will be saved on the UF Dropbox using a randomly generated number that corresponds with the participants’ medical record numbers.

The UF Dropbox cloud-hosting service will only be accessible to study personnel who require viewing the ECGs in order to assess them. Access to the UF Dropbox requires logging into the UF Health VPN and accessing the site via a password combination containing uppercase letters, lowercase letters, numbers, and punctuation. The KardiaMobile smartphone app requires either a 6-digit password login, fingerprint scan, or face ID to access. ECG recordings will not be permanently stored on the device hosting the recording and will be immediately transferred from the smartphone to the UF Dropbox.

Mobile ECGs will not contain any protected health information, and participants who volunteer to be a part of this research will only be identified by a number that corresponds to the number of persons the study is recruiting. For example, the first study volunteer will have their images labeled as “01” as well as “UF Health Clinic” and will have no personal health identifiers attached to their Mobile ECG recording.

The paper files collected will be stored in a secured holding unit after completion by study participants in accordance with the UF’s IRB guidelines. Upon notification of an irregular finding from the KardiaMobile single-lead device, the treating physician for the participant will be informed by research assistants. If the participant does not have a past medical history of arrhythmia, the physician will decide to order a 12-lead ECG to confirm any suspicion of cardiovascular disease.

The number of patients who were screened as having AFib and had an abnormal ECG reading will be compared by using the participant’s medical record on Epic Systems. The number of positive screens versus negative screens will also be compared to assess the sensitivity and specificity of testing in the given population.

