**Methods:**

Participants were recruited across 6 clinic sites across the University of Florida Health Network: University of Florida Health Nephrology, Sleep Center, Ophthalmology, Urology, Neurology, and Pre-Surgical. Participants, aged 18-99 years, who agreed to partake in the study were given a consent form and completed a questionnaire regarding their past medical history and risk factors for cardiovascular disease. Single-lead, 30-second ECGs were taken by the KardiaMobile ECG device. If patients are found to have newly diagnosed AFib, the attending physician is notified, and a 12-lead ECG or standard ECG equivalent will be ordered.

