### Procedure Flow Diagram

The procedure flow diagram is shown in Textbox 1.

Assessing the accuracy of the KardiaMobile smartphone–based electrocardiogram (ECG) system for atrial fibrillation pathology.Approach the patient with informed consent at the University of Florida Health Clinic:Yes: Proceed with smartphone-based ECG screenNo: Do not perform smartphone-based ECG screenClinic-specific screening surveySmartphone-based ECG screenCardiologist interprets ECG readings and order confirmatory 12-lead ECG if indicated

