### Outcome Measures

#### Overview

The following measures will be collected for all participants. All data will be stored via a secured, university-affiliated Dropbox account approved by the IRB, a HIPAA-compliant and university-supported app used for data capture and storage.

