#### Primary Measures

##### Detection Accuracy

The researchers will measure the accuracy of the KardiaMobile ECG device by comparing the resulting ECG phenotype (normal, possible AF, unreadable, unclassified, tachycardia, or bradycardia) to the patients’ actual heart health as determined by the standard 12-lead ECG.

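### The 12-lead reference is obtained selectively after an irregular Kardia finding, so the planned sensitivity and specificity are exposed to verification bias

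*Protocol article*

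**What the plan says.** **What is to be measured.** Under Primary Measures, Detection Accuracy compares each Kardia result category, including normal, with the patient's "actual heart health as determined by the standard 12-lead ECG". The Overview of Outcome Measures states: "The following measures will be collected for all participants". The Procedure section adds: "The number of positive screens versus negative screens will also be compared to assess the sensitivity and specificity of testing in the given population". Statistical Analysis lists sensitivity and specificity again.

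**Who gets the reference.** The Procedure section begins the pathway with the device result: "Upon notification of an irregular finding from the KardiaMobile single-lead device, the treating physician for the participant will be informed by research assistants". It continues: "If the participant does not have a past medical history of arrhythmia, the physician will decide to order a 12-lead ECG". The Procedure Flow Diagram has a cardiologist interpret the readings and "order confirmatory 12-lead ECG if indicated". The Abstract's Methods says that, after newly diagnosed AFib is found, "a 12-lead ECG or standard ECG equivalent will be ordered".

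**What else bears on it.** The Participants section requires no follow-up visit and keeps patients with known AFib in the study. The Procedure section also mentions the Epic medical record, but gives no rule for using it as the reference in screen-negative participants. Results reports 381 abnormal readings among 2,339 participants, still awaiting a cardiologist. Discussion nevertheless reports a sensitivity of 95% and a specificity of 97%.

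**The concern.** Sensitivity needs the number of people in AFib whom the device missed. Specificity needs the number of people without AFib whom it correctly passed. Most of both groups lie behind normal readings, and the article describes no systematic reference test there. Whether someone is verified depends on the result of the test under evaluation, which is partial verification. Counting positive against negative screens does not repair this: the counts give the positivity rate, not agreement with a reference.

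At stake is the accuracy half of specific aim 1. Followed as written, the plan yields a sensitivity that looks better than the device's true one whenever AFib hides behind normal readings, and a specificity among verified participants that looks worse. Discussion already uses the accuracy figures to support routine screening, and its limitations do not mention verification.

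**Working it through.** **1. The article's own figures.** The 95% and 97% cannot be reproduced. No 2×2 table, number verified or definition of a positive screen is given, and the 381 abnormal readings are described as unread by a cardiologist.

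**2. Inputs from Results.** Enrolled 2,339; abnormal 381, of which 78 possible AFib, 159 unclassified and 49 unreadable. I take one reading per participant.
- Not abnormal: 2,339 − 381 = 1,958, and 1,958/2,339 = 83.7%.
- Abnormal other than possible AFib: 381 − 78 = 303.

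**3. General form.** Let v1 and v0 be the shares of screen-positives and screen-negatives who receive the 12-lead.
- Observed sensitivity = TP·v1/(TP·v1 + FN·v0)
- Observed specificity = TN·v0/(TN·v0 + FP·v1)

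With an assumed true sensitivity of 70% and specificity of 97%:

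| v1 | v0 | Observed sensitivity | Observed specificity |
|---|---|---|---|
| 1 | 1 | 70% | 97% |
| 1 | 0.20 | 92.1% | 86.6% |
| 0.8 | 0.10 | 94.9% | 80.2% |
| 1 | 0.05 | 97.9% | 61.8% |
| 1 | 0 | 100% | 0% |

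Whenever v0 is below v1, sensitivity is too high and specificity too low.

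**4. Size at the data cut.** Count only possible AFib as positive. Assume that 40 of the 78 are confirmed and that the other 303 abnormal readings are verified and free of AFib. If a fraction f of the 1,958 were in AFib, true sensitivity = 40/(40 + 1,958f).

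| f | Missed cases | True sensitivity | Verified data show |
|---|---|---|---|
| 0.03% | 0.6 | about 98.5% | 100% |
| 0.1% | 2.0 | 95% | 100% |
| 0.5% | 9.8 | 80% | 100% |
| 1.3% | 25.5 | 61% | 100% |

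The lowest value follows from the 98.5% sensitivity that the Introduction cites for pharmacy patients: 40/0.985 − 40 = 0.6 missed, and 0.6/1,958 = 0.03%. The highest borrows the Introduction's figure for undiagnosed AFib in older patients. That is a population figure, not a rate after a normal strip, so it serves only as an upper illustration.

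**5. Specificity, and the definition of positive.** On the same assumptions, specificity among verified participants is 303/(303 + 38) = 88.9%. In the full sample, with none missed, it is (303 + 1,958)/(303 + 1,958 + 38) = 2,261/2,299 = 98.3%. If instead any abnormal reading is positive, and only abnormal readings are verified, the results are 100% and 0% by construction.

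**6. Relaxing the assumption on the 303.** If 2% or 5% of them were AFib (6.06 or 15.15 cases), verified-only sensitivity would be 40/46.06 = 87% or 40/55.15 = 73%. Adding 0.5% missed among the 1,958 (9.79 cases) gives true values of 40/55.85 = 72% and 40/64.94 = 62%. The bias is still upward.

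**7. Predictive value is only partly verified too.** If 30% of the 78 (23.4) had no 12-lead and 28 of the 40 true cases were confirmed, the value over all 78 would lie between 28/78 = 35.9% and (28 + 23.4)/78 = 65.9%.

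**The case against.** The strongest case on the other side is that the article does not rule out a reference for normal readings. The flow diagram has the cardiologist interpret readings without limiting this to abnormal strips, the Epic record is mentioned, the Overview speaks of all participants, and a reported sensitivity of 95% implies that some false negatives were counted. This stands to a degree. A reader might infer that normal readings can never be verified, that sensitivity and specificity cannot be estimated at all, or that sensitivity must come out at 100%. The documents support none of these. They show no systematic reference for screen-negatives. The 100% in step 4 needs the other 303 abnormal readings to be AFib-free, and step 6 shows what follows if they are not. Nor do the documents show that the 95% and 97% are false, only that their derivation is not given.

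Epic does not settle the matter. Charted AFib is not rhythm at screening, so using the chart as reference could bias results in either direction. Epic may, however, simply be where 12-lead results are retrieved, so its mention is not proof of a changed reference standard. An unstated interval between the Kardia strip and the 12-lead may be detail left to the full protocol, and I do not count it.

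A reader might also infer that treating all unverified participants as disease-free pushes both measures up. That fails when some positives are unverified. With TP 40, FP 38, FN 10 and TN 2,251, leaving 30% of positives unverified moves 12 true cases among the false positives. Apparent specificity is then 2,261/2,311 = 97.8%, against a true 2,251/2,289 = 98.3%.

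**Conclusion.** The point holds in this form: the primary accuracy measure rests on a 12-lead that the described pathway supplies selectively, and 83.7% of readings at the data cut have no systematic reference. Against the 12-lead, sensitivity is biased upward if any AFib lies behind normal readings, and specificity among verified participants is biased downward. The sensitivity distortion runs from negligible (true value about 98.5%) to large (61%) over missed-AFib rates of 0.03% to 1.3%. This rests on the assumed 40 confirmed cases, the assumed absence of AFib in the other abnormal readings, and possible AFib alone counting as positive. Results does not split these counts by arrhythmia history, so the illustration cannot be confined to the group the pathway covers. The design gives no basis for presenting 95% and 97% as study accuracy.

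**What to change.** - Define a positive screen, and state how unclassified and unreadable readings are handled.
- Make the headline measures the positive predictive value of a possible-AFib reading and the yield of confirmed new AFib per person screened, each with a 95% confidence interval, in participants without an arrhythmia history. Report beside them the share of positives actually verified, and bounds for the unverified positives.
- Report sensitivity and specificity only in participants whose 12-lead was obtained regardless of the Kardia result, such as existing 12-leads found in Epic. Otherwise report them as bounds over an assumed missed-AFib rate whose range includes values near zero.
- Do not present the 95% and 97% in Discussion as study accuracy on this design.
- Reconcile the Abstract, Procedure, Procedure Flow Diagram and Overview on who receives the 12-lead and who triggers it.

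The work is protocol and analysis wording plus an Epic query. The price is a weaker accuracy claim: predictive value and yield in place of sensitivity and specificity.

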### Procedure Flow Diagram

The procedure flow diagram is shown in Textbox 1.

Assessing the accuracy of the KardiaMobile smartphone–based electrocardiogram (ECG) system for atrial fibrillation pathology.Approach the patient with informed consent at the University of Florida Health Clinic:Yes: Proceed with smartphone-based ECG screenNo: Do not perform smartphone-based ECG screenClinic-specific screening surveySmartphone-based ECG screenCardiologist interprets ECG readings and order confirmatory 12-lead ECG if indicated

### Outcome Measures

#### Overview

The following measures will be collected for all participants. All data will be stored via a secured, university-affiliated Dropbox account approved by the IRB, a HIPAA-compliant and university-supported app used for data capture and storage.

#### Primary Measures

##### Detection Accuracy

The researchers will measure the accuracy of the KardiaMobile ECG device by comparing the resulting ECG phenotype (normal, possible AF, unreadable, unclassified, tachycardia, or bradycardia) to the patients’ actual heart health as determined by the standard 12-lead ECG.

##### Feasibility

Staff members from the different clinic sites will be asked how the incorporation of the mobile ECG device impacted the flow of the clinic. This will provide researchers with information on whether or not this study impacts the length of time it takes for patients to be seen by their physicians, informing us on the feasibility of implementing this device in a clinical setting.

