**Results:**

As of March 1, 2024, a total of 2339 participants have been enrolled. Of the data collected thus far, the KardiaMobile rhythm strip reported 381 abnormal readings, which are pending analysis from a cardiologist. A total of 78 readings were labeled as possible AFib, 159 readings were labeled unclassified, and 49 were unreadable. Of note, the average age of participants was 61 (SD 10.25) years, and the average self-reported weight was 194 (SD 14.26) pounds. Additionally, 1572 (67.25%) participants report not regularly seeing a cardiologist. Regarding feasibility, the average length of enrolling a patient into the study was 3:30 (SD 0.5) minutes after informed consent was completed, and medical staff across clinic sites (n=25) reported 9 of 10 level of satisfaction with the impact of the screening on clinic flow.

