### Specific Aims

The aim of this study is to demonstrate the feasibility of performing Kardia-enabled ECG recordings routinely in outpatient settings in high-risk populations and its potential use in uncovering previously undiagnosed cases of AFib. Specific aim 1 is to determine the feasibility and accuracy of performing routine cardiac rhythm sampling in patients deemed at high risk for AFib. Specific aim 2 is to determine whether routine rhythm sampling in outpatient clinics with high-risk patients can be used cost-effectively in an outpatient clinic without increasing the time it takes for the patient to be seen by a physician.

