## Methods

### Participants

For this study, we will recruit approximately 655 participants from each of the selected University of Florida (UF) outpatient specialty clinics. This sample size was specifically chosen as a result of statistical analysis that suggests this study population would indicate a powered study. There is no control group, as this was an observational study. Due to the nature of our enrollment process, which does not require a follow-up visit, we expect a <1% attrition rate, reaching a desired ~655 samples per site based on our power analysis. Study participants will be between the ages of 18 and 99 years.

Eligible participants are any patient visiting the UF Nephrology Clinic, UF Sleep Clinic, UF Neurology Clinic, UF Ophthalmology Clinic, UF Urology Clinic, and UF Pre-Surgical Center. Patients with a history of AFib will not be excluded from the study, as they provide valuable data on potential risk factors and may be prone to AFib recurrence. Participants were only excluded if they were younger than 18 years of age, a leg or hand amputee, a paralyzed person, unable to consent, or unable to read and comprehend English.

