### Statistical Analysis

The information collected from the study is categorical data: accurate versus inaccurate. We will be performing an interrater reliability test using Cohen κ coefficient for each of the individuals making a preliminary diagnosis. This will give us a level of agreement. All tests will be 2-sided, and *P* values <.001 will be considered statistically significant.

The number of participants required to achieve statistical significance for this study was calculated to be 655 after completing a power analysis for a 2×2 contingency table design. The probability of a positive diagnosis was .84 and .82 for KardiaMobile and standard ECG, respectively, after applying published literature findings on the efficacy of both methods. Applying Cohen κ statistic, we are looking at the agreement between the 2 metrics to see if KardiaMobile is an effective prescreen. Additional statistical methods include direct comparison, noninferiority, superiority, qualitative comparison, sensitivity, and specificity.

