## Discussion

A total of 2339 participants across 6 different medical specialty clinics were enrolled in this study. Preliminary findings of the feasibility and accuracy of performing routine cardiac rhythm sampling in patients deemed at high risk for AFib were encouraging, with the average length of patient enrollment being 3:30 (SD 0.5) minutes after informed consent was completed. This time included the participant filling out the site-specific questionnaire. The average length of the single-lead mobile ECG data collection was just 30 (SD 2.5) seconds. Furthermore, when considering feasibility, there were no reports from clinical staff regarding the patient enrollment effort impacting the flow of clinic operations, and 9 of 10 reported satisfaction with the study on clinic operations per medical staff (n=25). Regarding accuracy, the study demonstrated KardiaMobile to have a sensitivity and specificity of 95% and 97%, respectively, for detecting previously undiagnosed AFib. The relatively short time to collect the single-lead ECG along with the accuracy of the technology in detecting AFib suggests that the implementation of routine rhythm sampling with high-risk patients can be used cost-effectively in an outpatient clinic without increasing the time it takes for the patient to be seen by a physician.

The use of a single-lead mobile ECG strip can serve as a low-cost, effective AFib screen for implementation across outpatient clinics attempting to provide increased health care accessibility. A study published in 2022 suggested an “incremental cost-effectiveness ratio of US $57,894 per quality-adjusted life year, meeting the acceptability threshold of US $100,000 per quality-adjusted life year” regarding the cost-effectiveness of single-lead mobile ECGs [26,27]. Additionally, patients can easily purchase this device on their own and measure their ECG signal from the comfort of their own homes. This may allow for more immediate feedback on their heart health and a reduction in costs from clinic visits.

Limitations to the study include the fact that the study was not designed to measure the impact of potential moderators on the outcomes. Additionally, there were limitations related to the relatively high rates of unclassified or unreadable ECG outputs that have been included in the abnormal findings data. Furthermore, the participants were not asked to return for another reading, as these outputs are representative of the device’s effectiveness.

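### Aim 2 (cost-effective use with no longer wait for the physician) has no waiting-time measure, no cost measure and no comparator, yet the Discussion draws the conclusion

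*Protocol article*

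**What the plan says.** **The aim.** Specific Aims (and the Objective in the Abstract) sets aim 2: to determine whether rhythm sampling can be used cost-effectively in an outpatient clinic "without increasing the time it takes for the patient to be seen by a physician".

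**The measure.** Under Primary Measures, Feasibility, the protocol article says: "Staff members from the different clinic sites will be asked how the incorporation of the mobile ECG device impacted the flow of the clinic". It then states what the answers are for: "This will provide researchers with information on whether or not this study impacts the length of time it takes for patients to be seen".

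**The comparator.** Participants says: "There is no control group, as this was an observational study".

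**The analysis.** Statistical Analysis describes the data in one line: "The information collected from the study is categorical data: accurate versus inaccurate". The methods that follow concern agreement and accuracy.

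**The result and conclusion.** The Abstract reports that "medical staff across clinic sites (n=25) reported 9 of 10 level of satisfaction with the impact of the screening on clinic flow". The Discussion concludes that screening "can be used cost-effectively in an outpatient clinic without increasing the time it takes for the patient to be seen by a physician", and its closing paragraph repeats that screening is cost-effective and does not get in the way of clinic operations.

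**The concern.** The aim makes two claims. The first is comparative: time to be seen is no longer with screening than without it. That needs a time and something to compare it with. The second is economic, and needs at least the resources used and what was gained. The article names neither kind of data, and treats staff opinion as though it showed the effect on waiting time.

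At stake is half of the stated purpose. A clinic deciding whether to adopt the device would read the Discussion as saying that this study found no delay and good value. Following the plan would not reveal a real delay or a poor return, because nothing named in it would record either.

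**Working it through.** The article gives no sample size, margin or standard deviation for waiting time or cost, so there is no figure to reproduce. The sample size of 655 belongs to the comparison of KardiaMobile with standard ECG and does not bear on aim 2. The check sets what the aim needs beside what the article supplies.

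**Step 1. Named outcomes.** Outcome Measures has seven headings.

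| Heading | Waiting time? | Cost or resource use? |
|---|---|---|
| Detection Accuracy | no | no |
| Feasibility | no (staff opinion on flow) | no |
| Demographics | no | no |
| Symptoms | no | no |
| Risk Factors | no | no |
| Site-Specific Health | no | no |
| Heart Health | no | no |

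That is 0 of 7 for each part of the aim.

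**Step 2. Comparator.** Participants states that there is none, and no before-and-after or screened-versus-unscreened contrast is described. Even a recorded waiting time would therefore not show whether screening had lengthened it.

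**Step 3. What the Discussion argues from.**

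| Evidence offered | What it measures | Why it does not answer aim 2 |
|---|---|---|
| Staff satisfaction (n=25) and no staff reports of disruption | perceived flow | no minutes, no comparison |
| Enrolment, mean 3:30 minutes | procedure time after consent, questionnaire included | excludes consent; not time to be seen; no comparison |
| ECG recording, mean 30 seconds | procedure time | not time to be seen; no comparison |
| Accuracy of the device | test performance | neither a time nor a cost |
| US $57,894 per quality-adjusted life year | result of an outside 2022 study | not costs or effects in these clinics |

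The first three rows bear on feasibility in a broad sense. None is a waiting time. The only cost-effectiveness result is external.

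**Step 4. What a direct comparison would need (illustration only).** The article gives no spread for waiting time, so the standard deviation (SD) is assumed over a range. Take a difference of 3.5 minutes (the recorded enrolment time), two-sided alpha 0.05 and 80% power. Patients per condition:

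n = 2 × SD² × (1.960 + 0.842)² / 3.5² = 2 × SD² × 7.849 / 12.25

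- SD 10 minutes: 2 × 100 × 7.849 / 12.25 = 128.1, so 129
- SD 15 minutes: 2 × 225 × 7.849 / 12.25 = 288.3, so 289
- SD 20 minutes: 2 × 400 × 7.849 / 12.25 = 512.6, so 513
- SD 30 minutes: 2 × 900 × 7.849 / 12.25 = 1153.3, so 1154

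A non-inferiority comparison with a 3.5-minute margin, one-sided alpha 0.025 and no true difference gives the same numbers. They treat patients as independent; patients in one clinic session share its delays, so the true requirement would be larger.

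**The case against.** **Procedure time is relevant.** The recording takes place in the waiting room and lasts about 30 seconds. A short task done while patients are already waiting may well add no delay. This stands as indirect evidence, but the aim was to determine the effect, and the figure leaves out consent and has no comparison.

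**An article condenses a fuller protocol.** It reports timed durations that its own outcome list does not mention, so the list may not be complete. This stands to the extent that one can say only that no waiting-time or cost measure is named or reported here. It does not remove the problem: the article itself fixes the aim, the primary measure, what that measure is said to show, and the conclusion.

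**The conclusions are hedged.** The Discussion says that the findings suggest the result, and the closing paragraph calls the measures preliminary. That softens the wording, but a preliminary estimate still has to be an estimate of the quantity claimed.

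**Stronger readings that the article does not support:**
- A reader might infer that the conclusion rests on the 25 staff alone. The Discussion ties it to short ECG time and accuracy, and also cites the outside ratio.
- A reader might treat the staff result as a proportion of 25 people and put a confidence interval on it. The Abstract words it as "reported 9 of 10 level of satisfaction with the impact of the screening on clinic flow", which reads as a rating; the Discussion is ambiguous. A binomial interval does not apply to a rating.
- A reader might treat the absence of staff reports as none out of 25. The article gives no denominator for that statement.
- A reader might take the 381 abnormal readings as the follow-up workload. They include unclassified and unreadable outputs and await a cardiologist, and the 12-lead ECG depends on arrhythmia history and the physician's decision. They do not count triggered 12-lead ECGs.

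**Conclusion.** The point holds. As described in the article, aim 2 is not measured. Waiting time is inferred from staff opinion and procedure time without a comparator, and cost-effectiveness from the short ECG time, device accuracy and an outside study. One of two specific aims cannot be answered by following the plan, and the conclusion drawn on it goes beyond the data named.

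The size of any delay or cost is unknown and cannot be derived from the article. That does not mean that screening delays patients or is poor value; either answer remains open. The verdict assumes that no fuller document holds a waiting-time or cost measure that the article fails to mention. If one exists, the Feasibility section should name it as the measure for aim 2. Aim 1 is unaffected.

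**What to change.** **Main change (wording).** With 2339 participants already enrolled, this is the realistic route.
- *Specific Aims and Abstract:* restate aim 2 as describing how clinic staff perceive the effect of screening on clinic flow, and how long enrolment and recording take.
- *Feasibility:* remove the claim that staff answers show the effect on time to be seen. State the question and response scale, so that the 9 of 10 result has one meaning.
- *Discussion, including its closing paragraph:* remove cost-effectiveness and absence of added waiting time as findings of this study. Keep the outside ratio as background only, and say wherever the 3:30 minutes appears that it excludes consent.

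This costs editing time and a more modest conclusion.

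**Optional addition, if check-in and physician-start timestamps prove to be available.** The article mentions Epic only as the source of participants' medical records, so availability must be checked first. Compare clinic sessions with and without screening, because non-participants in the same session may share any delay. Report the difference in minutes with a 95% confidence interval, and count device cost, staff minutes and triggered 12-lead ECGs. This costs a data extract, and review-board agreement should be checked, since the consent described covers participants only. The comparison would not be randomised, so differences between sessions could bias it.
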